### **5.4 CTEPH versus non-CTEPH diagnosis**

CTEPH versus non-CTEPH diagnosis will be made by the principal or subinvestigator. To diagnose CTEPH, concordant findings must be present on V/Q scintigraphy, organised thrombi must be identified within the pulmonary arteries on at least one modality (CT pulmonary angiography or catheter-based pulmonary angiography), and pulmonary hypertension must be confirmed by right heart catheterisation. Because this trial is focused on diagnosing pulmonary perfusion impairment, the strict duration of anticoagulant therapy (usually 3 months) is not included as a requirement for diagnosis in this trial. The CTEPH versus non-CTEPH diagnosis will be determined within 42 days after registration.

### **5.5 End of testing (EoT)**

Registered subjects will reach the end of testing (EoT) upon completion of dynamic chest radiography and V/Q scintigraphy. After the principal or subinvestigator determines the diagnosis of CTEPH versus non-CTEPH, all required information will be entered into the electronic data capture (EDC) system without omissions. Adverse events will be collected in relation to dynamic chest radiography. If a serious adverse event occurs, appropriate measures prioritising patient safety will be taken. In the event of discontinuation, the prespecified assessments at discontinuation will be performed as far as possible within 7 days, and the date and reason for discontinuation will be recorded. Serious adverse events will be reported appropriately in accordance with Section 8 (Adverse events and malfunctions).

### **5.6 Randomisation, end of study (EoS) and image reading**

After registration, once the subject reaches EoT and the principal or subinvestigator has determined the diagnosis of CTEPH versus non-CTEPH, the data manager will confirm that there are no missing data in the EDC system. Using an allocation tool, cases will be stratified by the final diagnosis so that the numbers of CTEPH and non-CTEPH cases are balanced between the two reading groups and will then be allocated 1:1 to (i) the initial work-up-only

reading group and (ii) the initial work-up plus pulmonary circulation analysis image reading group. After allocation, the case reaches end of study (EoS). For cases allocated to each group, a reading ID will be assigned so that the group can be identified by the image interpretation committee. Information (initial work-up data) will be sent to image readers, excluding the final diagnosis. For all cases, pulmonary circulation analysis images will be created from dynamic chest radiography acquired by the investigational device (see the appendix “Procedure for creating analysis images from dynamic chest radiography”). Trained readers in the image interpretation committee will interpret the images (see Section 13 Image interpretation committee; the SOP for operating the image interpretation committee; and the SOP for image interpretation). Reading results, including the initial discrimination result of CTEPH versus non-CTEPH by the image interpretation committee, will be sent to the statistical analyst, and the endpoints will be calculated.

The trial will be considered completed when all enrolled cases have reached EoS and all related trial procedures have been completed.

[figure not shown]

## Study flow (primary analysis)

[figure not shown]

**Reader study outline (blinded core laboratory: primary and secondary outcomes, and inter-reader variability assessment)**

**5.7 Endpoints and rationale**

In this trial, image evaluations will be conducted by an independent image interpretation committee. The composition of the independent committee and the method for determining evaluation outcomes are specified in Section 13 (Image interpretation committee).

**5.7.1 Primary endpoint**

Diagnostic accuracy (Sensitivity, Specificity, positive predictive value and negative predictive value will also be assessed as secondary endpoints) for initial discrimination between CTEPH and non-CTEPH in the intention-to-treat (ITT) population, comparing the group of the standard initial work-up alone versus the device -added group.

**5.7.2 Secondary endpoints**

- Comparison of sensitivity, specificity, positive predictive value and negative predictive value for initial discrimination between CTEPH and non-CTEPH between the group of the standard initial work-up alone versus the device -added group in the ITT population.
- Agreement (kappa coefficient) between the pulmonary circulation analysis program and perfusion scintigraphy regarding the presence of regional perfusion defects in each of six lung regions.

[figure not shown][figure not shown][figure not shown]

| Right                                    | Left                                     |
|------------------------------------------|------------------------------------------|
| Upper:
Perfusion defect
( + / - )  | Upper:
Perfusion defect
( + / - )  |
| Middle:
Perfusion defect
( + / - ) | Middle:
Perfusion defect
( + / - ) |
| Lower:
Perfusion defect
( + / - )  | Lower:
Perfusion defect
( + / - )  |

| Right                                              | Left                                               |
|----------------------------------------------------|----------------------------------------------------|
| Upper:
Segmental perfusion defect
( + / - )  | Upper:
Segmental perfusion defect
( + / - )  |
| Middle:
Segmental perfusion defect
( + / - ) | Middle:
Segmental perfusion defect
( + / - ) |
| Lower:
Segmental perfusion defect
( + / - )  | Lower:
Segmental perfusion defect
( + / - )  |

[figure not shown]

Kappa coefficient for agreement in six area

- Performance evaluation of dynamic chest radiography/pulmonary circulation analysis program for discriminating CTEPH versus non-CTEPH using perfusion scintigraphy as the reference standard: sensitivity, specificity, accuracy, PPV and NPV, in accordance with the STARD 2015 guideline.

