### **5.3.2 Six-region assessment of perfusion defects on perfusion scintigraphy**

For perfusion scintigraphy, technetium-99m macroaggregated albumin (99mTc-MAA) will be administered, and lung perfusion images will be acquired using a gamma camera SPECT system or SPECT/CT system. Multi-direction planar images (including anterior and posterior views; two views are acceptable) and SPECT images will be obtained; where available, CT images for fusion will also be acquired.

Six-region assessment (image interpretation committee): Using SPECT/CT (or SPECT when CT is unavailable) to define the cranio-caudal extent of the lungs, each lung will be divided into three equal zones (upper, middle and lower), resulting in six zones in total. A reference anterior planar image with six-zone division lines will be created for scoring. For each of the six zones, readers will record “present” when an embolic-type perfusion abnormality is judged to be present and “absent” when it is judged not to be present. Ventilation scintigraphy is not used for this six-region assessment; therefore, V/Q mismatch is not considered in this analysis.

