#### **7.1.5 Diagnosis**

After completion of the above examinations, the principal or subinvestigator will determine the diagnosis of CTEPH or non-CTEPH according to the diagnostic criteria below.

- CTEPH: all of the following are met:
  - 1) V/Q scintigraphy: segmental defects or multiple subsegmental defects on perfusion imaging.
  - 2) CT pulmonary angiography and/or catheter-based pulmonary angiography: findings of organised thrombi in the pulmonary arteries.
  - 3) Right heart catheterisation: pulmonary hypertension, defined as mPAP >20 mmHg at rest and pulmonary vascular resistance  $\geq$ 3 Wood units.
- Non-CTEPH: does not meet the criteria for CTEPH above.
  - a) A definitive diagnosis other than CTEPH is made (pulmonary hypertension clinical classification).

- b) Right heart catheterisation shows mPAP  $\leq 20$  mmHg (no pulmonary hypertension).
- c) An appropriate diagnosis cannot be made or appropriate images/data are not available, and the principal/subinvestigator judges the case to be inappropriate for evaluation in this trial.

Note: The definition of pulmonary hypertension is based on the 2022 ESC/ERS Guidelines, where pulmonary hypertension is defined as mPAP  $>20$  mmHg. Therefore, mPAP  $>20$  mmHg and pulmonary vascular resistance  $\geq 3$  Wood units are used in the diagnostic criterion in this protocol.

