### **13.3 CTEPH/non-CTEPH determination in the secondary endpoint (pulmonary circulation analysis program images)**

For one secondary endpoint, the same five readers as in the primary endpoint will interpret dynamic chest radiography/pulmonary circulation analysis images in the intervention group to determine CTEPH/non-CTEPH. In this evaluation, the determination will be made by majority vote among the five readers.

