### **13.4 Determination of regional perfusion defects (six-region assessment)**

For the six-region assessment, each lung is divided into upper, middle and lower regions (six regions in total). Each region will be assessed for the presence or absence of a perfusion defect on pulmonary circulation analysis images and on perfusion scintigraphy images.

Pulmonary circulation analysis images will be interpreted by the same five internal medicine physicians as in the intervention group. Perfusion scintigraphy images will be interpreted by three nuclear medicine physicians from CTEPH expert centres. All designated readers will interpret all cases. The final presence/absence of a regional perfusion defect for each region will be determined by majority vote.

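### A secondary endpoint labelled CTEPH versus non-CTEPH is scored against perfusion scintigraphy, which supplies only one of the trial's three CTEPH criteria

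*Protocol*

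**What the plan says.** Protocol 5.7.2 lists as its third secondary endpoint "Performance evaluation of dynamic chest radiography/pulmonary circulation analysis program for discriminating CTEPH versus non-CTEPH using perfusion scintigraphy as the reference standard". It is to be reported as sensitivity, specificity, accuracy, PPV and NPV under STARD 2015.

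The trial's own definition of the disease is in 7.1.5: "CTEPH: all of the following are met". The three criteria are:

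- "V/Q scintigraphy: segmental defects or multiple subsegmental defects on perfusion imaging"
- "CT pulmonary angiography and/or catheter-based pulmonary angiography: findings of organised thrombi in the pulmonary arteries"
- "Right heart catheterisation: pulmonary hypertension, defined as mPAP >20 mmHg at rest", together with a pulmonary vascular resistance threshold.

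Section 5.6 requires the investigator's diagnosis to be settled before a case is allocated to a reading group.

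On who reads what, 13.3 says that "the same five readers as in the primary endpoint will interpret dynamic chest radiography/pulmonary circulation analysis images in the intervention group", with the call decided by majority of the five. Section 13.4, on the six-region assessment by the same five readers, says "All designated readers will interpret all cases". Section 5.6 has analysis images created for every case in both groups.

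**The concern.** The named target and the named reference are different things. Scintigraphy can show the first criterion of 7.1.5; it cannot show organised thrombi or raised pulmonary pressure. A patient with perfusion defects but without one of the other two criteria is non-CTEPH by the trial's definition and positive by this endpoint's reference.

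In such a patient a correct negative call from the device is counted as a missed case, and a wrong positive call is counted as a hit. The result would still be published as CTEPH sensitivity and specificity. It would also be on a different scale from the accuracy of 0.92 cited in 10.1, which is 46/50 against the clinical diagnosis.

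A second, smaller matter is precision. If 13.3 is applied as worded, the image-only call is made in about half of the cases that have analysis images.

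**Working it through.** **Inputs (Protocol 1.5 and Table 2; 50 patients, 29 CTEPH and 21 non-CTEPH)**

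- V/Q positive: 32, of whom 29 had CTEPH (29/29 sensitivity, 29/32 PPV).
- Device positive: 31, of whom 28 had CTEPH (28/29 sensitivity, 28/31 PPV).
- Device–V/Q agreement 0.90, kappa 0.79. I take the agreement as patient-level in all 50, so 45/50.

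**Step 1. Rebuild the device-by-V/Q table.** Let *a* be the number positive on both. Both negative is then 50 − 32 − 31 + *a* = *a* − 13. Agreement requires *a* + (*a* − 13) = 45, so *a* = 29. The only solution is:

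| | V/Q + | V/Q − |
|---|---|---|
| Device + | 29 | 2 |
| Device − | 3 | 16 |

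**Step 2. Check against the stated kappa.** Chance agreement is 0.64 × 0.62 + 0.36 × 0.38 = 0.5336. Kappa = (0.90 − 0.5336)/(1 − 0.5336) = 0.786, which reproduces the stated 0.79.

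**Step 3. Score the same device reads against each reference.**

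| | Against diagnosis | Against V/Q | Change |
|---|---|---|---|
| Sensitivity | 28/29 = 96.6% | 29/32 = 90.6% | −6.0 points |
| Specificity | 18/21 = 85.7% | 16/18 = 88.9% | +3.2 points |
| Accuracy | 46/50 = 92.0% | 45/50 = 90.0% | −2.0 points |

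**Step 4. See where the shift comes from.** V/Q was positive in all 29 CTEPH patients, so all 28 true device positives are in the both-positive cell. The 29th patient there is non-CTEPH: one shared false positive (29 − 28 = 1). V/Q was falsely positive in 32 − 29 = 3 patients, so in the other 2 the device was correctly negative. Against V/Q, those 2 correct calls become misses and the 1 shared error becomes a hit. Hence 29/32 is (28 + 1) hits over (29 + 3) reference positives.

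**Step 5. Range if the retrospective rates held in this trial.** Let π be the CTEPH share (0.41 observed or 0.50 assumed in 9.1). Both tests have false-positive rate 3/21 = 0.143, device sensitivity is 28/29, V/Q sensitivity is 1, and *o* is the joint false-positive rate among non-CTEPH patients, unknown, from 0 to 0.143.

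- Apparent sensitivity = [π × 0.966 + (1 − π) × *o*] / [π + (1 − π) × 0.143]. For π = 0.41 it runs from 0.80 (*o* = 0) to 0.97 (full overlap); for π = 0.50, from 0.85 to 0.97 (0.845 to 0.970).
- Apparent specificity = (1 − 0.143 − 0.143 + *o*) / (1 − 0.143), from 0.83 to 1.00.

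The answer therefore depends heavily on how far the errors of the two tests coincide, which is not a property of CTEPH discrimination.

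**Step 6. Precision from 54 or 108 cases.** Assume a 50:50 case mix, sensitivity near 0.966 and no attrition. Wilson 95% intervals for sensitivity:

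- Intervention group only, 26/27: 82–99%.
- All cases, 52/54: 87–99%.

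At 41% CTEPH the Clopper–Pearson intervals are 77–100% (21/22) and 88–100% (43/44).

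**The case against.** *The reference is stated openly, and performance against the diagnosis is already covered.* The primary endpoint and the first secondary endpoint assess CTEPH discrimination, with allocation stratified by the final diagnosis. Under 7.1.6 a regional defect on the analysis images forces a CTEPH call, so the device arm is largely device-driven. This stands as a limit on importance: a reader might infer that the trial never measures the device against the clinical diagnosis, and that would be wrong. It does not justify the CTEPH label here. The device does image perfusion, but that argues for the separate six-region kappa endpoint.

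*The reference may not be the ventilation-free read.* Section 5.3.2 says "Ventilation scintigraphy is not used for this six-region assessment; therefore, V/Q mismatch is not considered in this analysis", but only of the six-region assessment. Section 7.1.3 has ventilation imaged and mismatch recorded, and discrimination criteria are referred to an image interpretation SOP that is not at hand. It is tempting to say that this endpoint's reference ignores ventilation; the protocol does not establish that. The mismatch remains either way, because even full V/Q is one criterion of three.

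*Section 13.3 may not restrict the cases.* Its mention of the intervention group could identify the readers, as a similar phrase does in 13.4, and 5.7.2 names no population. Restriction is the plain reading but not the only one.

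*The six-point figure is selective and fragile.* Fair. Specificity moves the other way, accuracy changes by two points, and the Wilson intervals for 28/29 (83–99%) and 29/32 (76–97%) overlap widely. Those reads were radiologist consensus compared with full V/Q; here internists are compared with perfusion scintigraphy.

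*The majority vote is a legitimate choice.* Agreed. A reader might infer that it makes the endpoint wrong because it overstates one physician's performance. The size of any overstatement rests on reader accuracies and correlations that no document gives, and 13.2 already takes a single reader's judgement for the primary endpoint.

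**Conclusion.** The endpoint is wrong as written: it names CTEPH discrimination as its target and sets a reference that cannot determine CTEPH under 7.1.5. This is not a detail left to the SAP, because the protocol itself fixes the reference.

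In the only data the protocol offers, the choice of reference is worth 6.0 points of sensitivity, 3.2 of specificity in the other direction, and 2.0 of accuracy. These figures assume that the reported agreement is patient-level in all 50 patients, which the kappa supports. They show that the two references are not interchangeable. They do not show that the device is less sensitive than reported, nor forecast this trial's result.

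The restriction in 13.3 is a secondary matter of wording and lost precision, conditional on the plain reading. The primary endpoint and the planned 108 cases are unaffected.

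**What to change.** 1. In 5.7.2, make the final diagnosis of 7.1.5 the reference standard for this endpoint.
2. Report the comparison with perfusion scintigraphy as agreement on perfusion defects: kappa with positive and negative agreement. In the retrospective data the latter two would be 2 × 29/(32 + 31) = 92.1% and 2 × 16/(18 + 19) = 86.5%. Do not call these CTEPH sensitivity and specificity.
3. In 13.3, state that all cases with usable analysis images, from both groups, are read for the image-only CTEPH call.
4. Make that call separately from the six-region read, or after the six-region read is locked. Section 5.3.1 excludes the static radiograph from the six-region read, while Sections 1.4 and 4 have the analysis images interpreted together with it.
5. Optionally, show single-reader results beside the majority vote.

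The cost is protocol and SAP wording, plus one additional call on analysis images and static radiograph per reader for about 54 control-group cases. The diagnosis is already required for every case before allocation, so no new examination is needed.

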### 5.7.3 Exploratory endpoints

- Subgroup analyses in the primary endpoint according to sex (male vs female): comparison of accuracy, sensitivity and specificity between the group of the standard initial work-up alone versus the device -added group.

- Subgroup analyses in the primary endpoint according to obesity (BMI  $\geq 25$  kg/m^2 vs BMI  $< 25$  kg/m^2): comparison of accuracy, sensitivity and specificity between the group of the standard initial work-up alone versus the device -added group.

- Subgroup analyses in the primary endpoint according to pulmonary vascular resistance ( $> 4.0$  Wood units vs  $\leq 4.0$  Wood units): comparison of accuracy, sensitivity and specificity between the group of the standard initial work-up alone versus the device -added group.

- Subgroup analyses in the primary endpoint according to NT-proBNP ( $\geq 300$  pg/mL vs  $< 300$  pg/mL): comparison of accuracy, sensitivity and specificity between the group of the standard initial work-up alone versus the device -added group.

- Subgroup analyses in the primary endpoint according to peak tricuspid regurgitation velocity (greater than the median vs  $\leq$  the median): comparison of accuracy, sensitivity and specificity between the group of the standard initial work-up alone versus the device -added group.

- Subgroup analyses in the primary endpoint according to cardiac rhythm (sinus rhythm vs non-sinus rhythm): comparison of accuracy, sensitivity and specificity between the group of the standard initial work-up alone versus the device -added group.

- Subanalysis 1: comparison of accuracy, sensitivity, specificity, PPV and NPV between the control and intervention groups stratified by reader experience (more than 5 years vs 5 years or less) in the ITT population and in the full analysis set (FAS).

- Examination time (time spent in the examination room), radiation dose (dose area product [DAP], only in facilities able to measure it) and number of acquisitions including repeats when acquiring dynamic chest radiography for the pulmonary circulation analysis program in the ITT population and FAS.

- Exclusion proportion of pulmonary circulation analysis images reconstructed from dynamic chest radiography in the ITT population and FAS (including reasons for exclusion, e.g., failure to acquire dynamic chest radiography, failure of analysis by the program, or images judged inappropriate by investigators).

### 5.7.4 Safety endpoint

Adverse events during dynamic chest radiography and device malfunctions during the trial period.

## 6 Participant registration

### 6.1 Registration procedures

The principal or subinvestigator will obtain written informed consent from subjects judged likely to be eligible for this trial. Each consented subject will be assigned a subject identification code, which will be recorded and managed in the subject identification code list. After confirming that the subject meets all inclusion criteria and none of the exclusion criteria, the investigator will register the case using the case registration function of the electronic data capture (EDC) system. If there are questions regarding eligibility criteria, the investigator should confirm with the coordinating investigator.

EDC system: cubeCDMS.

For inquiries regarding the registration procedure and use of the EDC system: Micron, Inc. ([contact]; business hours: 9:00-17:00).

For inquiries regarding inclusion/exclusion criteria: Coordinating investigator [name] (Department of Cardiovascular Medicine, Kyushu University Hospital; [contact]; e-mail: [contact]).

### 6.2 Precautions at registration

- Dynamic chest radiography should be performed after registration; however, if dynamic chest radiography has been performed between screening and registration, those images may be used in lieu of post-registration imaging.
- The interval between dynamic chest radiography and perfusion scintigraphy must be within 14 days.
- Registration will not be accepted until eligibility is confirmed based on data entered into the EDC system.
- A registered subject will not have their registration cancelled except in the event of withdrawal of consent that includes refusal to allow use of data for the trial.
- In the event of duplicate registration, the information from the first registration (e.g., registration number) will be adopted.
- If erroneous registration or duplicate registration is identified, the investigator should promptly contact the point of contact described in Section 6.1 (Registration procedures).

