**Table 5. Study schedule**

|                     | Informed consent | Screening | Registration | Examination    |                   |                | Allocation /image reconstruction | End of study (EoS)     |
|---------------------|------------------|-----------|--------------|----------------|-------------------|----------------|----------------------------------|------------------------|
| Visit window        | Day - 28 ~ Day 0 |           | Index Day 0  | Day 0 ~ Day 28 | Day - 28 ~ Day 42 | Day 0 ~ Day 42 |                                  | Within 7 days from EoS |
| Informed consent    | ○                |           |              |                |                   |                |                                  |                        |
| Eligibility         |                  |           | ○            |                |                   |                |                                  |                        |
| Enrollment          |                  |           | ○※1          |                |                   |                |                                  |                        |
| Patients background |                  | ○         |              |                |                   |                |                                  |                        |
| Height/weight       |                  | ○         |              |                |                   |                |                                  |                        |

|                                                 |  |     |  |     |     |     |   |   |
|-------------------------------------------------|--|-----|--|-----|-----|-----|---|---|
| WHO functional class                            |  | ○   |  |     |     |     |   |   |
| Blood test                                      |  | ○※2 |  |     |     |     |   |   |
| ECG                                             |  | ○※2 |  |     |     |     |   |   |
| Pulmonary function test                         |  | ○※2 |  |     |     |     |   |   |
| UCG                                             |  | ○※2 |  |     |     |     |   |   |
| Chest X-ray                                     |  | ○※2 |  |     |     |     |   |   |
| Dynamic chest radiography                       |  |     |  | ○※3 |     |     |   |   |
| V/Q scintigraphy / SPECT-CT                     |  |     |  | ○※3 |     |     |   |   |
| Right heart catheterisation                     |  |     |  |     | ○※2 |     |   |   |

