| Final CTEPH/non-CTEPH diagnosis by investigator |  |     |  |     |     | ○※2 |   | ○ |
| Adverse events                                  |  |     |  | ○   |     |     |   | ○ |
| Malfunction                                     |  |     |  | ○   |     |     | ○ |   |

\* Items marked with an asterisk (\*) constitute the standard initial work-up information.

※1 Dynamic chest radiography should be performed within 28 days after registration; however, if performed between screening and registration, those images may be used.

※2 Right heart catheterisation should be performed within 28 days after registration; however, if performed within 180 days before registration, those data may be used.

EoT: End of testing; EoS: End of study.

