### **8.4 Evaluation of malfunctions**

For malfunctions that occur during use of the investigational device, the following will be recorded as applicable: malfunction name; date and time of occurrence; situation of the malfunction; contributing factors (if any); whether any harm occurred; severity; seriousness; causal relationship with the investigational device; serial number of the investigational device; whether any action was taken for the malfunction (and details if yes); and whether there is a risk of a serious adverse event due to the malfunction.

Malfunctions related to the investigational device include poor image quality or program operational failures when using the pulmonary circulation analysis program. For malfunctions occurring during the trial period, the malfunction name, date and time of occurrence, situation and contributing factors (if any) will be recorded.

If a malfunction is judged to potentially lead to a serious adverse event as defined in Section 8.2.1, the principal investigator will report it in the same manner as a serious adverse event in accordance with Section 8.5.

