### **10.2.4 Safety analysis set (SAS)**

The SAS is defined as all registered subjects excluding those in whom dynamic chest radiography was not acquired even once.

Analysis populations will be finalised before database lock at a case review meeting. If issues not described here need to be considered for specific cases, the decision will be made at the case review meeting.

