### **10.3.3 Safety analysis**

Adverse events and malfunctions will be summarised in the SAS.

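### Dynamic chest radiography may precede registration, but the safety set holds only registered subjects, so anyone imaged early and then not registered is left out of the safety summary

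*Protocol*

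**What the plan says.** All references are to the protocol.

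- **Timing of imaging.** Sections 5.3 and 6.2 place DCR after registration. Section 6.2 then makes an exception: "if dynamic chest radiography has been performed between screening and registration, those images may be used in lieu of post-registration imaging". A footnote to Table 5 repeats it: "if performed between screening and registration, those images may be used".
- **Registration can fail.** Under Section 6.2 a subject is not accepted until eligibility has been confirmed from the data in the EDC system. Under Section 5.2 enrolment ends at 108 registered patients. Under Section 17.1 a subject may withdraw at any time.
- **Safety set.** Section 10.2.4: "The SAS is defined as all registered subjects excluding those in whom dynamic chest radiography was not acquired even once". Section 10.3.3: "Adverse events and malfunctions will be summarised in the SAS". No other safety population is defined.
- **Safety endpoint.** Section 5.7.4: "Adverse events during dynamic chest radiography and device malfunctions during the trial period". Registration is not mentioned.
- **Recording and reporting.** Section 5.5 collects adverse events in relation to DCR. Section 8.2 requires details of any event related to the procedure to be recorded, and Section 8.5 requires serious ones to be reported. None of the three sets registration as a condition of the rule.
- **Schedule.** From registration onward, the window row of Table 5 reads "Index Day 0 | Day 0 ~ Day 28 | Day - 28 ~ Day 42 | Day 0 ~ Day 42". DCR is marked in the Day 0 to Day 28 column. Adverse events are marked there and at end of study; malfunctions are marked there and under allocation/image reconstruction. Neither row has a mark under consent, screening or registration.

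**The concern.** A safety population should contain everyone who received the intervention. Here the intervention can be delivered while the subject is still unregistered, and entry to the SAS depends on a later administrative step that may not follow. The summary required by Section 10.3.3 could then omit exposed subjects from both numerator and denominator, so it would not fully estimate the endpoint in Section 5.7.4. The schedule has a related gap: a site working from Table 5 has no scheduled adverse-event or malfunction entry for a session held before Day 0.

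At stake is the completeness of the safety table. Efficacy is not involved.

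**Working it through.** **1. Route out of the safety set**

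| Step | Section | Condition |
|---|---|---|
| DCR acquired before registration | 6.2, Table 5 footnote | Permitted as an exception |
| Subject then not registered | 5.2, 6.2, 17.1 | Possible: ineligible, enrolment closed, or withdrawn |
| Subject in SAS? | 10.2.4 | No: the set begins with registered subjects |
| Event or malfunction summarised? | 10.3.3 | No: the summary uses the SAS only |
| Within the safety endpoint? | 5.7.4 | Yes: it follows the procedure and the trial period |

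The last two rows disagree. The disagreement comes from rules the protocol has already fixed, so a statistical analysis plan that follows Section 10.2.4 would inherit it.

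**2. Subjects imaged early and later registered**

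The SAS has no time limit. It asks only for registration and at least one acquisition, so these subjects are in it. For them the only gap is the Table 5 collection window. Table 5 can show a window that opens before Day 0: the right heart catheterisation column starts at Day -28. The column holding DCR, adverse events and malfunctions starts at Day 0, and only the DCR footnote reaches further back.

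**3. Size**

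The protocol gives no rate of non-registration and no share imaged early, so there is no stated figure to reproduce for this point. The registered total is 108 (Section 10.1: 102/0.95 = 107.4, set at 108). The rest is assumption.

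Let f be the share of consented subjects not registered and g the share of those imaged first. Assume all 108 registered subjects are imaged.

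- Not registered: U = 108 × f/(1 − f). For f = 5%, 10%, 20% this gives 5.7, 12 and 27.
- Exposed but outside the SAS: X = g × U.
- Share of all exposed: X/(108 + X).

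| f | g = 10% | g = 50% | g = 100% |
|---|---|---|---|
| 5% | 0.6 (0.5%) | 2.8 (2.6%) | 5.7 (5.0%) |
| 10% | 1.2 (1.1%) | 6.0 (5.3%) | 12 (10%) |
| 20% | 2.7 (2.4%) | 13.5 (11.1%) | 27 (20%) |

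The range is about 1 to 27 subjects. The right-hand column requires every unregistered subject to have been imaged first, which fits poorly with an exception.

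**4. Effect on a zero-event result**

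With no events in n subjects, the one-sided 95% upper bound is 1 − 0.05^(1/n). For n = 108 it is 2.7%; for n = 108 + 27 = 135 it is 2.2%. Omitting event-free subjects therefore changes little. The omission matters only if an omitted subject had an event or malfunction.

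**The case against.** The strongest reply is that nothing is lost at source. Sections 5.5, 8.2 and 8.5 attach recording and serious-event reporting to the procedure, so an event in an imaged but unregistered subject should still be recorded and, if serious, reported. A reader might infer that such events disappear from the trial altogether; the text does not support that. The gap is in the summary population.

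The schedule can also be read generously. The adverse-event and malfunction marks share a column with DCR, so they may be meant to move with the examination when it is brought forward. That is a fair reading, but the footnote moves only the images and says nothing of the two safety rows.

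Section 10.2.4 sends issues not described in the protocol to a case review meeting before database lock. This is a weak remedy here, because the restriction to registered subjects is described.

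Three stronger readings are tempting and should not be drawn:

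- **That poor early images make registration less likely and so bias the malfunction rate downwards.** DCR image quality is not among the criteria in Sections 3.1 and 3.2. Section 8.4 is also narrower than it first looks: "Malfunctions related to the investigational device include poor image quality or program operational failures when using the pulmonary circulation analysis program". Section 5.6 describes analysis images as created in the post-allocation process, so an unregistered subject's images may never reach the program. Any numerical contrast of malfunction rates would have to assume the excess it set out to show.
- **That a site may re-image after registration and leave the first session out.** Section 7.1.2 requires the number of acquisitions including repeats, with reasons, and Section 5.7.3 makes that count an endpoint. The allowance in Section 6.2 lets earlier images stand in for later ones; it does not permit a session to go unrecorded.
- **That the SAS covers only exposure from Day 0.** It has no such limit, as shown above.

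**Conclusion.** The point holds in a limited form. Sections 6.2, 10.2.4 and 10.3.3 together leave a consented subject who is imaged before registration and then not registered out of the safety summary, while Sections 5.5, 5.7.4, 8.2 and 8.5 follow the procedure or the trial period. Separately, the adverse-event and malfunction rows of Table 5 do not match its footnote on early imaging.

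This conclusion rests on the text alone. The size does not: 1 to 27 subjects is an assumed range, and the likely number is small because imaging after registration is the rule. The examination is non-invasive, so events should be few. No direction of bias can be claimed from the document. The primary analysis is untouched. Severity: minor.

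**What to change.** 1. In Section 10.2.4, define the SAS as all consented subjects with at least one DCR acquisition, whether or not they were later registered. Section 6.1 already gives each consented subject an identification code. Subjects who withdraw and refuse use of their data stay excluded under Section 12.4.
2. In Table 5, start the adverse-event and malfunction rows at the first DCR acquisition, including one made before Day 0.
3. Carry the same SAS definition into the statistical analysis plan, and report the number imaged but not registered.

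The cost is a wording change in two places and a short log or EDC entry for imaged subjects who are not registered. The downside is a few extra records. The sample size, the primary analysis and the imaging procedure do not change.
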